			**Expert panel**			
			**Emergency care**	**Outpatient care**		
			*Emergency (immediate or as soon as possible)*	*As soon as possible*	*Within 24 h*	> *24 h*
**SmED-Patient**	**Emergency care**	*Emergency (immediate or as soon as possible)*	Appropriate	Appropriate but too cautious	Appropriate but too cautious	Appropriate but too cautious
	**Outpatient care**	*As soon as possible*	Inappropriate and potentially hazardous	Appropriate	Appropriate but too cautious	Appropriate but too cautious
		*Within 24 h*	Inappropriate and potentially hazardous	Inappropriate and potentially hazardous	Appropriate	Appropriate but too cautious
		> *24 h*	Inappropriate and potentially hazardous	Inappropriate and potentially hazardous	Inappropriate and potentially hazardous	Appropriate

Legend: Care levels = bold and underlined; treatment time = italics

The expert panel’s assessment is based on the SmED-Patient recommendation, the patient’s complete medical history from the ED, and the clinical data from the hospital documented both in the study database using REDCap and through pseudonymized copies of clinical documents (e.g., lab results, physician’s letter). The expert panel assessments are performed using REDCap. After the physician experts have reviewed their share of cases, an interim analysis is performed to detect any discrepancies in [1] rating regarding care level and treatment time, and [4] rating regarding hazards to patient safety between the two experts. Criteria for inclusion in the case conference are: a) a discrepancy between one expert and the other in identifying the perfect level of care and treatment time as resulting from the combination of “emergency care + emergency”, “outpatient care + as soon as possible”, “outpatient care + within 24 h” or “outpatient care + > 24 h”; and b) a discrepancy in the categorization of a case as “inappropriate and potentially hazardous” by one expert and “appropriate” or “appropriate but too cautious” by the other (Table 7). In the event of these discrepancies, a case conference is held with the participation of another expert, who acts as a moderator, to seek agreement on the discrepant ratings.

It should be noted that experts are independent physicians who will be remunerated for their contributions.

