### Trial design {8}

The study is a prospective, multicentre cohort study of adult self-referred patients in the ED to assess the accuracy of the SmED-Patient recommendation as compared to an expert panel (gold standard). A parallel mixed-methods approach is chosen to compare, integrate and validate the research results through triangulation for inclusion of different data sources, data methods and conceptual perspectives [22].

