An expert panel (blinded to the SmED patient's recommendation) will recommend the level of care for each case, before the expert panel is presented with the SmED patient’s recommendations for the level of care to assess the appropriateness and risk of the recommendation for the patient’s safety (see Table 7). The comparison between SmED-Patient and SmED-Contact +, the latter conducted by a provider, provides additional validation of patient self-assessment with SmED-Patient.

SmED is a Class IIB medical product certified according to the Medical Device Directive (MDD). The study is conducted in accordance with the Declaration of Helsinki and relevant principles of ICH-GCP. ISO 14155 has been considered where applicable (informed consent, data protection, certified training for SmED-Contact + users), though full compliance is not required as SmED is used within its intended use.

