### Outcomes {12}

#### Primary outcome

Accuracy, measured as percentage of the perfect agreement in the assessment of the binary level of care between SmED-Patient and the expert panel for patients who self-referred to the ED.

SmED-Patient gives recommendations to the level of care in the following categories (see also Table 2):Emergency Medical Service (EMS),Hospital Emergency Department (ED),Registered outpatient care physician,Teleconsultation.

For the purposes of the study, the categories are combined into two levels, as these reflect the sectoral separation and empirically existing levels of care in Germany:Emergency Care: ED, EMSOutpatient Care: Registered outpatient care physician, teleconsultation (performed by a registered outpatient care physician).

The primary endpoint will be operationalized as a comparison of the level of care recommended by SmED-Patient and the expert panel for each case (see Table 3). Given that directing patients to the most appropriate level of care is the central purpose of algorithms like SmED, the primary endpoint of this study focuses on the perfect agreement between the recommendations of SmED-Patient and the expert panel in terms of binary care level only. The recommended time to treat will be examined as a secondary endpoint, as it is primarily relevant for patients with complaints suitable for outpatient care [10].

**Table 3 Tab3:** Operationalization of the perfect agreement assessment

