#### Module 2: expert panel assessment of SmED-Patient recommendation for all cases

An independent expert panel, consisting of primary care physicians (n=2) and physicians working in the ED (n=2), evaluates all valid cases in pairs.The cases will expectedly be divided equally between the pairs, with each case being evaluated independently by two experts. First experts are blinded to the SmED-Patient recommendations and only provided with the initial clinical patient data (routine ED and hospital data). Based on these data the experts provide (1) their own rating of perfect care level and treatment time along the evaluation matrix and (2) their rating of a range of appropriateness of the combination of care levels and treatment times along the evaluation matrix (Table 7). Thereafter the experts are unblinded to SmED-Patient recommendations and evaluate (3) the appropriateness of the SmED-Patient recommendation and (4) potential hazards to patient safety by the SmED-Patient recommendations, both in comparison to the perfect care level and time based on their former rating and the range of appropriate combinations of level of care and treatment time.

**Table 7 Tab7:** Range of appropriateness for SmED-Patient recommendations assessed by an expert panel

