### Interim analyses {21b}

An interim analysis is performed in Module 2 after both physician experts have reviewed all cases to identify any discrepant assessments of the primary endpoint (perfect level of care) and the secondary endpoint patient safety, that require a consensus process with a third expert in a case conference.

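### The conference that settles split care-level ratings comes after the experts have seen the SmED-Patient result, so the primary agreement can be biased in those cases

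*Protocol article*

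**What the plan says.** The primary outcome is "Accuracy, measured as percentage of the perfect agreement in the assessment of the binary level of care between SmED-Patient and the expert panel". The panel is the reference standard: Trial design {8} describes the aim as "to assess the accuracy of the SmED-Patient recommendation as compared to an expert panel (gold standard").

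Module 2 (under {18a}) sets out four ratings per expert. Ratings (1), the ideal care level and time, and (2), the range of acceptable combinations, are given blinded. The next step is: "Thereafter the experts are unblinded to SmED-Patient recommendations and evaluate (3) the appropriateness of the SmED-Patient recommendation", together with (4), the hazard to patient safety.

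The search for disagreement follows the review: "After the physician experts have reviewed their share of cases, an interim analysis is performed to detect any discrepancies in [1] rating" (1) and in rating (4). Discrepant ratings go to a case conference moderated by a further expert. Interim analyses {21b} repeats the order. The check takes place "after both physician experts have reviewed all cases to identify any discrepant assessments of the primary endpoint (perfect level of care") and of patient safety.

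Intervention description {11a} says that the blinded panel "will recommend the level of care for each case, before the expert panel is presented with the SmED"-Patient result. Module 2 also says, without limiting it to particular ratings, that the panel's "assessment is based on the SmED-Patient recommendation" as well as on the clinical record.

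**The concern.** In an accuracy study the reference standard should be fixed without knowledge of the index test. Here that is true of each expert's own rating. It is not true of the panel's final answer when the two experts differ, because the order of steps puts the conference after unblinding.

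The affected cases are few in kind but influential. The endpoint is binary, so when one expert says emergency care and the other outpatient care, SmED-Patient matches exactly one of them. The conference outcome then determines whether the case is scored as agreement or mismatch. By that point both experts know which answer agrees with the tool and have each judged whether its recommendation was hazardous. If this knowledge pulls the consensus towards the tool, measured agreement rises with no gain in accuracy, and the test against 58.5% is no longer held at its planned error rate.

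**Working it through.** **Order of steps.**

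1. Ratings (1) and (2) are given blinded (Module 2).
2. The recommendation is revealed, and ratings (3) and (4) are given (Module 2).
3. Discrepancies in (1) and (4) are identified after the review is complete (Module 2 and {21b}).
4. A conference seeks agreement on the discrepant ratings (Module 2).

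Rating (4) exists only after unblinding, so a check that covers (1) and (4) must follow unblinding. The article mentions no re-blinding, no earlier conference on (1) and no blinded moderator. The statement in {11a} fits step 1 but not step 4.

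**Which cases can move the primary endpoint.** Conference criterion (a) covers any difference across four care-and-time combinations. Three of these are outpatient timing categories, and a split among those three leaves the binary care level unchanged. Only an emergency-versus-outpatient split matters. Where both experts agree on care level, the reference rests on two independent blinded ratings.

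**The plan's own figure.** Inputs from Sample size {14} and {20a}: n = 150 evaluable, null value 58.5%, expected 70%, one-sided alpha 0.025, power over 80%, 25% dropout.

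- The smallest k with P(X ≥ k | 150, 0.585) ≤ 0.025 is k = 100, with exact error 0.0248. For k = 99 it is 0.0364.
- Power is P(X ≥ 100 | 150, 0.70) = 0.837, consistent with the stated figure.
- The rule that the lower 95% confidence limit must exceed 58.5% gives the same cutoff. At 100/150 the limit is 0.5852 (Clopper-Pearson), 0.5879 (Wilson) or 0.5912 (Wald), and 99/150 fails on all three.
- 150 / (1 − 0.25) = 200 enrolled.

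The sample size reproduces and is not in question. At the null, 150 × 0.585 = 87.75 agreements are expected, so 100 − 87.75 = 12.25 cases separate the null from success.

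**Effect of a shift.** Let d be the share of cases with a binary split and s the net shift of conference outcomes towards SmED-Patient, as a proportion of those cases. Then

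observed agreement = blinded agreement + d × s.

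The article gives neither d nor s, so the values below are assumptions. Blinded agreement is set at 58.5%.

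| d × s (assumed) | Net shift | Cases in 150 | Observed agreement | P(X ≥ 100) |
|---|---|---|---|---|
| none | 0 points | 0 | 58.5% | 0.025 |
| 10% × 10 points | 1 point | 1.5 | 59.5% | 0.043 |
| 20% × 10 points | 2 points | 3 | 60.5% | 0.071 |
| 20% × 20 points | 4 points | 6 | 62.5% | 0.166 |
| 30% × 20 points | 6 points | 9 | 64.5% | 0.322 |
| 30% × 30 points | 9 points | 13.5 | 67.5% | 0.623 |

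**The case against.** The strongest defence is that blinding is built in where it counts most. Each expert commits to a care level before seeing the tool's answer, and ratings (3) and (4) are judged against that earlier commitment. An expert who has already committed may well hold to that view in the conference. Neither the frequency of binary splits nor any pull towards SmED-Patient can be taken from the document. All of this stands. It limits the reach and the certainty of the bias, but it does not make the conference blinded.

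Four stronger readings are tempting and are not supported:

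- **That every conferenced case is compromised.** Disputes over outpatient timing alone cannot change the binary endpoint.
- **That the 2.5% error rate is lost.** That would need known values of d and s. Small values give 4% to 7%.
- **That care level and hazard are settled in one joint sitting.** Module 2 speaks of a case conference and Recruitment {15} of case conferences in the plural. Neither says that both items are settled together.
- **That the blinded ratings were meant to rest on presentation-time data only, in conflict with the full record described later.** Module 2 says the experts are "only provided with the initial clinical patient data (routine ED and hospital data"), so hospital data belong to the blinded stage on its own terms. The word initial is loose, but restricting the data would redefine a reference standard that the study chose deliberately.

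**Conclusion.** The point holds as a sequencing fault. For cases split on emergency versus outpatient care, the reference value for the primary endpoint is settled by experts who know the SmED-Patient result, contrary to the blinded panel recommendation described in {11a}. Bias towards SmED-Patient is the likely direction but is not proven.

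The size cannot be derived from the document. On the assumed shifts of 1 to 9 points, the chance of declaring success at a true blinded agreement of 58.5% is about 4% to 62%. A net movement of 3 cases in 150 already takes it to about 7%. The supportable conclusion is that the nominal 2.5% is no longer guaranteed. Because the primary reference standard is involved, and the same experts cannot give a blinded consensus on a case once they have seen the result, the order should be corrected before expert review starts.

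**What to change.** Split Module 2 into two locked stages.

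1. Collect ratings (1) and (2), run the discrepancy check, and hold the conference on (1) with experts and moderator blinded to SmED-Patient. Lock the consensus in REDCap.
2. Release the recommendation, collect (3) and (4), and hold a conference on (4) only.

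Align {11a}, Module 2 and {21b} with this order. Amend the Module 2 sentence that bases the panel's assessment on the SmED-Patient recommendation so that it applies to ratings (3) and (4) only.

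If review has already begun, keep the pre-conference blinded ratings. Report a sensitivity analysis of the primary endpoint with binary-discordant cases counted once as agreement and once as mismatch, alongside the concordant-only result. Neither part replaces a blinded consensus:

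- The two counts differ by the whole discordant share. At an assumed 20% to 30% that is 30 to 45 of 150 cases, more than the 12-case margin.
- The concordant-only analysis drops the borderline cases. It leaves 120 to 105 patients, with exact power at 70% agreement of about 69% to 67%.

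The sample size, cutoff, power, experts and cases do not change. The cost is REDCap form order, a second sitting, and experts returning to cases. That has to fit the fixed expert compensation in Recruitment {15} and the project end of 31.03.2026 in Trial status.

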#### Module 3: qualitative assessment of provider utility and implementation scenarios

The aim of the focus groups is to obtain a qualitative assessment of the utility and applicability from a healthcare provider perspective for two different models of emergency care. It aims to deepen the understanding of the healthcare provider perspective through a dynamic exchange of perspectives and needs between different healthcare professions regarding a hypothetical implementation of SmED-Patient in two different emergency care models.

In addition, multiple context-sensitive implementation scenarios will be identified and documented. Participants will also be asked to relate ideas for potential improvement in the application of SmED-Patient in the ED. Two focus groups (*n* = 5 each) are planned for this study. Focus groups will be guided by a semi-structured interview guideline, allowing participants to discuss their experiences, challenges, and perceptions of SmED-Patient and its potential implementation in the ED setting. The focus group interview guideline will be developed through an iterative process, drawing on the literature from implementation studies [31, 32], as well as the experience of the research group. Focus groups are led and moderated by a member of the research team.

Focus groups will be recorded and transcribed verbatim, with data analysed using qualitative content analysis [33]. Results will be reported according to the standards for reporting qualitative research guideline [34].

#### Module 4: microsimulation study and qualitative assessment of implementation scenarios (feasibility)

The identified implementation scenarios for SmED-Patient in the ED from the focus groups (module 3) will be converted into a simulation script by the study team. The microsimulation takes place as a filmed enactment by and with study personnel and students in the study group’s facilities and has no impact on routine ED operations. Enacted patients will not be familiarized with the use of SmED-Patient prior to the microsimulation. The evaluation of the filmed microsimulation will be carried out in a final workshop where the microsimulation will be screened and all participants of the previous focus groups (*n* = 5–10) will be invited to discuss the following questions and provide context for their assessments:Does the filmed microsimulation match the suggested implementation scenario by the focus groups (scenario translation)?Does the use of SmED-Patient in the ED setting appear realistic regarding ED workflow and patient-provider interactions (realism)?Does the use of SmED-Patient in the ED setting appear feasible regarding workflow integration (feasibility)?Does the use of SmED-Patient in the ED setting appear beneficial for ED workflows and patient-provider consultations (benefit)?

The goal of the microsimulation is the quasi-realistic simulation of the implementation of SmED-Patient in the ED and its qualitative evaluation by the participants of the focus groups (module 3). The final workshop will be audio-recorded and supplemented with notes from the research team members guiding the workshop and observing participants’ reactions to the filmed microsimulation. The analysis follows the approach described in module 3.

Table 8 provides an overview of the schedule of events and assessments in modules 1–4 of the study.

**Table 8 Tab8:** Schedule of enrolment, interventions and assessments

Timepoint	Study period											
	**Module 1 (patient survey)**									**Module 2 (expert panel)**	**Module 3 (focus group interviews)**	**Module 4 (micro-simulation)**
	**Screening**	**Baseline**				**Treatment**		**Follow-up**				
	*** − t1***	***t0-1***	***t0-2***	***t0-3***	***t0-4***	***t1 (nurse enconter)***	***t2 (physician encounter)***	***t3 (post-discharge)***	***t4 (retro-spectively)***	***t5***	***t6***	***t7***
**Eligibility**												
Eligibility screening	X											
Informed consent	X									X	X	X
**Interventions**												
Primary data (part 1)		X										
Randomization of order of SmED assessments + SmED assessments			X									
Primary data (part 2)				X								
Primary data (part 3)					X							
Nurse assessment						X						
Physician assessment									X			
Expert panel										X		
Focus group interviews											X	
Microsimulation												X
Usual care						X	X					
**Assessments**												
Baseline variables		X										
Demographics	X	X										
SmED assessments			X									
Nurse assessment						X						
Primary outcome			X							X		
Secondary outcomes		X	X	X	X				X		X	X
Routine clinical data								X				

*t* Timepoints of study measure, *SmED* Structured Initial Medical Evaluation Assessment Germany (German: Strukturierte Medizinische Ersteinschätzung Deutschland)

#### Module 5: data triangulation and integration

The objective of the module is to triangulate the data from modules 1 to 4, with a view to advancing the interpretation and integration of the findings as well strengthening their validity from different stakeholder perspectives. In particular, the evaluation of the benefits to patients with different social characteristics and providers of different professional backgrounds of using SmED-Patient within the context of the ED will be analysed. This will allow us to draw inferences about the overall benefits of using the system in acute and emergency care. In order to achieve this, a mixed-methods matrix will be constructed [35], combining the results of the qualitative and quantitative data collection on the respective endpoints (i.e. patient and provider utility) to ascertain the overall benefit and the emerging themes.

### Plans to promote participant retention and complete follow-up {18b}

The study period for each participant ends after t0. No follow-up is required.

### Data management {19}

The study group will be provided with a web-based research application by the Zi. This application contains a demo version of both SmED-Patient and SmED-Contact +. This ensures an independent test of the applications without interfering with the live results, which the Zi collects online from users of the SmED-Patient configuration “Patient Navi” (https://www.116117.de/de/patienten-navi.php). Assessment results and assessment IDs can be retrieved from the SmED research application and linked to primary and secondary data at a later stage. The primary and secondary data will be documented in an electronic case report forms (eCRF) using the REDCap database, which is hosted on the internal servers of the Charité—Universitätsmedizin Berlin. Upon reasonable request, aggregate data will be provided.

The study complies with the General Data Protection Regulation (GDPR). All data will be pseudonymized to allow linkage with the assessment results from SmED-Patient and SmED-Contact + as well as the expert panel reviews. All data will be stored on a secure, restricted university server with access limited to study personnel. The study’s data management plan has been reviewed and approved by the Clinical Trials Office, an independent body of Charité – Universitätsmedizin Berlin.

### Confidentiality {27}

Access to the trial data at participating study sites will be limited to the principal investigator and authorized study team members. Recruitment logs will be securely stored in locked cabinets at the local sites. Following the guidelines of the German Research Foundation, data will be archived for a period of 10 years [36].

### Plans for collection, laboratory evaluation and storage of biological specimens for genetic or molecular analysis in this trial/future use {33}

Not applicable.

## Statistical methods

### Statistical methods for primary and secondary outcomes {20a}

Two-sided 95% confidence intervals are calculated for the proportion of perfect agreement on the binary care level (primary endpoint). The primary null hypothesis is rejected if the lower bound of the confidence interval is greater than 58.5%. In addition to the primary endpoint measure, the kappa measure is calculated to assess the agreement between SmED-Patient and the expert panel.

The statistical analysis will be multifocal in accordance with the stated endpoints. All data will be analysed using the Statistical Package for Social Sciences (IBM SPSS V 30.0.0.0 [171]). Descriptive analysis includes the presentation of relative and absolute frequencies for categorical variables and the calculation of median and interquartile range (non-normal) or mean and standard deviation (normal). The agreement of SmED ratings between SmED-Contact + and SmED-Patient is performed using the Intraclass Correlation Coefficient (ICC) similar to Cohen’s Kappa to measure the level of agreement between the two sets of recommendations.

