### Intervention description {11a}

The software “Strukturierte medizinische Ersteinschätzung in Deutschland” (SmED) is designed to assist in determining the appropriate time to treat (see Table 1) as well as the most appropriate point of care (see Table 2). Tables 1 and 2 provide an overview of the urgency and care levels defined by the SmED manufacturer (manufacturer: in4medicine AG, Bern, Switzerland; Importer: Health Care Quality Systems [HCQS], Göttingen, Germany).

**Table 1 Tab1:** Level of urgency according to “time to treat” and corresponding treatment recommendations

Time to treat	Name	Recommended action
1	Emergency	CPR readiness. There is a potentially life-threatening condition. Medical treatment must be given now.
2	Immediately	Medical treatment does not allow any delay. Treatment should be given immediately.
3	Today	Medical treatment does not have to take place immediately. Medical treatment should take place within the next 24 h.
4	Later	Medical treatment is not urgent. If the symptoms do not subside in the next 2 days, treatment by a physician is indicated.

Legend: *CPR* Cardiopulmonary resuscitation

**Table 2 Tab2:** Level of care according to “point of care” and corresponding treatment recommendations

Point of care	Name	Recommended action
1	EMS	Medical treatment should be provided by the Emergency Medical Service (EMS).
2	Hospital/ED	Medical treatment should be provided at a hospital in an ED.
3	Physician	Medical treatment should be provided by a registered outpatient care physician.
4	Tele-consultation	The person concerned should be advised in a teleconsultation on how to proceed.

Legend: *ED* Emergency department, *EMS* Emergency medical service

Participants in the multicentre cohort study will be assessed by study personnel using SmED-Contact + and asked to self-assess their symptoms using SmED-Patient. The order of the assessments is randomized. The assessments are conducted using a tablet, with the assessments being processed and stored in a web-based study entity provided by the Central Institute for Statutory Health Insurance in the Federal Republic of Germany (Zi).

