#### Secondary outcomes

The secondary outcomes are as follows:Symptom assessment overlap and utility: Assessment of recommendation and symptom assessment by SmED-Patient compared to a retrospective physician assessment and the utility of SmED-Patient in the ED (physician assessment in a sub-sample of *n* = 30–60 cases; based on an adapted version of a validated assessment sheet [10]).Agreement of SmED ratings: Percentage of agreement between the recommendations of SmED-Patient and SmED-Contact +.Patient safety and appropriateness: Percentage of cases in which the SmED-Patient recommendation is judged by the experts to be appropriate, appropriate but too cautious, or inappropriate and potentially hazardous (judged according to a range of appropriateness) (see Table 7).Patient assessment of urgency: Percentage of disagreements between patients’ self-assessed urgency and SmED-Patient assessed urgency (see Table 4).Patient utility: Evaluation of utility, including comprehensibility, usability, confidence with responses, response time, satisfaction, trust and hypothetical compliance as well as preparedness for the medical consultation. Subgroup analysis: Investigation of aspects that influence patients’ assessment of SmED-Patient, e.g. health literacy, age.Provider utility: Qualitative evaluation of the utility, including practical utility and perceived benefits of the SmED-Patient short report and of SmED-Patient (full assessment) by ED personnel in focus groups.Feasibility: Qualitative assessment of the feasibility of implementing SmED-Patient in the ED setting.

**Table 4 Tab4:** Overview of target variables and corresponding survey instruments

Target variable	Instrument
Reasons for ED presentation	Measured using an instrument designed by the research group to identify reasons and motives (see Additional file 1)
Patients’ assessment of urgency	Measured using SmED’s categorization of urgency: 1) Emergency (Immediately); 2) As soon as possible; 3) Within 24 h; 4) More than 24 h [13]
Health literacy	HLS19-Q12 (sub-dimension for coping with illness, items 1 to 4) [23], HLS19-COM-P-Q6 (short version) [24]
Sources of information for symptom assessment prior to ED presentation	Measured using an adapted instrument tested within the research group [25]
Medical care received for presented symptom(s) prior to ED presentation	Measured using an adapted instrument tested within the research group [25]

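### Agreement between SmED-Patient and SmED-Contact + is defined as a percentage, but the only analysis named for it is an ICC, which does not estimate that percentage

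*Protocol article*

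**What the plan says.** All references are to the protocol article.

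- **Outcome.** Secondary outcomes, under Outcomes {12}, gives this endpoint as "Percentage of agreement between the recommendations of SmED-Patient and SmED-Contact" +. It does not say whether the recommendation meant is point of care, time to treat, their combination or the binary care level.
- **Analysis.** Statistical methods {20a}: "The agreement of SmED ratings between SmED-Contact + and SmED-Patient is performed using the Intraclass Correlation Coefficient (ICC"), described in the same sentence as "similar to Cohen’s Kappa to measure the level of agreement between the two sets of recommendations". Neither the numerical coding nor the scale is given.
- **Scale.** Primary outcome: "SmED-Patient gives recommendations to the level of care in the following categories", followed by EMS, ED, outpatient physician and teleconsultation. Table 1 in {11a}, titled "Level of urgency according to “time to treat” and corresponding treatment recommendations", has four ordered steps.
- **Grouping.** Under Primary outcome, "the categories are combined into two levels, as these reflect the sectoral separation and empirically existing levels of care in Germany": EMS with ED on one side, physician with teleconsultation on the other.
- **Parallel comparison.** For SmED-Patient against the expert panel, {20a} uses the percentage on the binary level with a 95% confidence interval, plus kappa.

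**The concern.** The outcome section and the analysis section name different quantities. A percentage of agreement is read directly. An ICC is a ratio of variances: it needs numbers, and its value depends on how far apart those numbers are.

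For point of care this matters, because the study itself treats the distances as unequal. An EMS/ED difference is no difference at all once the categories are grouped, whereas an ED/physician difference crosses the boundary that defines a mismatch in Table 3. On codes 1 to 4, an ICC gives both the same weight.

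Section {11a} presents the comparison with SmED-Contact + as further validation of patient self-use. A single high coefficient on four codes could stand in for that validation while disagreement across the emergency/outpatient boundary stayed out of sight. A coefficient on that scale could also not be set beside the binary percentage and kappa planned for the expert panel.

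**Working it through.** The plan states no expected value or precision for this comparison, so there is no figure of its own to reproduce. The tables below are constructed. Only the number of pairs, 150 (Sample size {14}), comes from the plan; margins and swap counts are assumptions.

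**Formulas.** For n patients rated by k = 2 versions, ICC(A,1) = (MSR − MSE) / (MSR + MSE + 2(MSC − MSE)/n), with mean squares for patients, versions and residual. Kappa = (Po − Pe)/(1 − Pe).

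**1. Four care levels, margins 20/55/55/20 for both versions, 22 swaps (11 each way) between two adjacent codes.**

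- Both means are 2.5, so MSC = 0.
- Total sum of squares: 2 × (40 × 2.25 + 110 × 0.25) = 235.
- Each one-step swap adds 1²/2 = 0.5 within patients: 22 × 0.5 = 11, so MSE = 11/149 = 0.0738.
- MSR = (235 − 11)/149 = 1.5034.
- ICC = (1.5034 − 0.0738)/(1.5034 + 0.0738 − 2 × 0.0738/150) = 0.907.

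The calculation does not ask which adjacent codes were swapped:

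| Measure | EMS/ED swaps only | ED/physician swaps only |
|---|---|---|
| Four-level ICC | 0.907 | 0.907 |
| Four-level agreement | 128/150 = 85.3% | 85.3% |
| Four-level unweighted kappa | 0.789 | 0.789 |
| Binary agreement | 100% | 85.3% |
| Binary kappa | 1.00 | (0.853 − 0.5)/0.5 = 0.707 |

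Four-level kappa uses Pe = (20² + 55² + 55² + 20²)/150² = 0.304. With margins 12/63/63/12 the ICC is 0.872 for both patterns. Its level moves with the margins; the equality does not.

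**2. Spacing, at a fixed 80% four-level agreement** (margins 37/38/38/37, 30 swaps, 15 each way; total sum of squares 2 × (74 × 2.25 + 76 × 0.25) = 371).

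- Swaps one step apart: within-patient sum 15, MSR = 356/149 = 2.389, MSE = 15/149 = 0.101, ICC 0.920.
- Swaps EMS/teleconsultation, three steps apart: within-patient sum 30 × 9/2 = 135, MSR = 236/149 = 1.584, MSE = 135/149 = 0.906, ICC 0.274.
- The EMS/ED table with codes 2 and 3 exchanged: within-patient sum 30 × 4/2 = 60, MSR = 311/149 = 2.087, MSE = 60/149 = 0.403, ICC 0.678.

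Four-level percentage (80%) and unweighted kappa (0.733) are the same in all three.

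**3. Direction, on two levels.** With 30 disagreements in 150 pairs (60 agreements in each category), all one way or all the other way, the ICC is 0.617 both times, kappa 0.615 both times and agreement 80% both times. None of the three shows direction.

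**4. Skewed margins, on two levels, 128 agreements.** The balanced table (64, 11, 11, 64) gives ICC 0.708 and kappa 0.707. The skewed table (4, 11, 11, 124) gives ICC 0.186 and kappa 0.185. The two coefficients fall together.

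**5. What the defined quantity would deliver.** For 128/150, the Wilson 95% interval is (0.8533 + 0.0128 ± 1.96 × √(0.000834 + 0.0000427))/1.0256, or 78.8% to 90.1%.

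**The case against.** The strongest defence is that the plan can be read benignly. Section {20a} likens the ICC to Cohen's kappa and also promises: "Descriptive analysis includes the presentation of relative and absolute frequencies for categorical variables". Agree/disagree is a categorical variable, so its percentage may well be reported with the ICC beside it. The scale of the ICC is open: on the binary level it nearly equals kappa (0.708 against 0.707 above) and could be compared with the expert-panel result. On ordered time to treat, an ICC is close to quadratic-weighted kappa (0.920 against 0.919 in the one-step table of step 2), so it is not an invalid choice there. Coding and ICC form may sit in an analysis plan that is not shown.

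Most of this stands, and it rules out several stronger readings that a reader might infer:

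- *That blindness to the type or direction of disagreement is a defect of the ICC alone.* Steps 1 and 3 show that percentage and unweighted kappa on the same scale share it.
- *That the ICC should give way to kappa because it falls with skewed margins.* Step 4 shows that kappa falls equally.
- *That the protocol fixes the ICC on codes 1 to 4.* It names no scale, so the four-level result is conditional.
- *That patient safety would go unexamined.* The grading into "appropriate, appropriate but too cautious, or inappropriate and potentially hazardous" is made against the expert panel (Table 7), not between the two SmED versions.

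The mismatch itself remains. The general line on frequencies does not name this endpoint, the one sentence that does names a different quantity, and that choice is made in the protocol rather than left to a later document.

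**Conclusion.** The point holds as a mismatch between a secondary outcome and its named analysis. The outcome is a percentage; the ICC does not estimate it. If the ICC is run on the four care-level codes, it depends on their spacing (0.27 to 0.92 at a fixed 80% agreement in the tables tried) and returns one value for binary agreement of 100% and of 85.3%. These sizes rest on constructed tables, since the documents give no expected cell counts; the equality between the two swap patterns needs only equal margins and equal numbers of one-step swaps.

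The case for change rests on reporting the defined percentage on the binary level, not on any general superiority of kappa over the ICC. No hypothesis, threshold or sample size is attached to this outcome, and the primary test against 58.5% is unaffected.

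**What to change.** In {20a}, replace the ICC sentence with three statements:

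1. The main analysis of agreement between SmED-Patient and SmED-Contact + is the percentage agreement on the binary care level with a 95% confidence interval, accompanied by Cohen's kappa, as for the expert panel.
2. For the ordered time-to-treat categories, percentage agreement is reported with weighted kappa, with the weights stated. Quadratic weights would give nearly the value that an ICC would have given.
3. The full cross-tables are shown, so that the direction of disagreement and swaps within a care level are visible. McNemar's test on the binary level is optional.

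Name the same scales in the definition under Secondary outcomes. The cost is a few lines of text: no new data, no change to sample size, and a simple run on the recommendations already collected.
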